#### Missing Data

Missing data will be examined to determine whether information is missing at random by comparing participants with and without missing data. If no significant differences are observed in key demographics, missing at random will be assumed. If missingness exceeds 5%, we will use multiple imputation methods to impute missing responses. Sensitivity analyses will be conducted to assess the impact of the imputed data.

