### Participants

#### Population

This study plans to recruit 440 older adult participants aged 50 years or older, with at least 50% over the age of 65, and with approximately 50% of the sample being male. We will try to achieve the balanced ratio by monitoring sample demographics throughout the study and adjusting recruitment techniques as needed to target necessary demographics. Among these, 330 participants will be seeking to start MM treatment during the study period, as indicated at baseline when they are enrolled in the study, and 110 participants will have no intention of starting MM treatment for at least 6 months. However, participants are free to initiate or stop MM use at any time during the study and continue participation after they join the study. If a participant decides to withdraw from the study or is lost to follow-up at any point, data will be analyzed up to the point of withdrawal.

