### Limitations

There are several limitations to our study. Patients can obtain an MM card as early as the same day they meet with a qualifying physician, which may limit the ability to enroll participants prior to the initiation of MM treatment. Conversely, some participants in the MM group, despite expressing an intention to start treatment promptly, may experience delays in initiation due to various barriers, such as financial constraints or access issues. To address this issue, we have implemented additional compensation for participants who delay the initiation of their MM treatment to enroll in the study and begin MM treatment within 4 weeks of their baseline visit. Another potential limitation of the SMILE study is the wide variety of MM products and modes of administration available. As this is an observational study, no limitations are placed on what types of products may be used by participants. Attrition bias is a concern, as study participants who experience side effects or receive no benefits from MM treatment may withdraw from the study, which could result in a more favorable outcome toward MM improving chronic pain. To prevent this, our team emphasizes to the participants that we would like to continue monitoring their health outcomes regardless of whether they continue using MM. Our team may also waive certain data measures (eg, EMA, Fitbit) to make participation easier for individuals who are considering withdrawing from the study. Additionally, individuals with chronic pain may be experiencing pain due to undiagnosed cancer, which could result in misclassification.

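### A non-significant comparison of demographics cannot justify assuming missing at random, and it cannot detect the outcome-driven dropout that the protocol itself expects

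*Protocol article*

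**What the plan says.** The Missing Data section sets out four steps.

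- Purpose and method: "Missing data will be examined to determine whether information is missing at random by comparing participants with and without missing data".
- Criterion: "If no significant differences are observed in key demographics, missing at random will be assumed".
- Imputation trigger: "If missingness exceeds 5%, we will use multiple imputation methods to impute missing responses".
- Check on the result: "Sensitivity analyses will be conducted to assess the impact of the imputed data".

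The section gives no instruction for the case where demographics do differ. Under Population, for anyone who withdraws or is lost to follow-up, "data will be analyzed up to the point of withdrawal".

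The Limitations section names the dropout it fears: "Attrition bias is a concern, as study participants who experience side effects or receive no benefits from MM treatment may withdraw from the study". It also gives the direction: "which could result in a more favorable outcome toward MM improving chronic pain". The remedies listed there concern retention: stressing continued follow-up whether or not MM use continues, and waiving burdensome measures. None concerns the analysis. Power and Sample Size plans for 20% attrition.

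**The concern.** MAR is a statement about the outcomes nobody saw: given what was observed, missingness does not depend on them. Observed data cannot test that. A comparison of age, sex and similar variables can at most contradict missing completely at random with respect to those variables, and a non-significant result does not show that even they are balanced.

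The mismatch with Limitations is what makes this more than loose wording. The expected mechanism works through response and side effects, which demographics need not reflect. The check can pass while dropout favours MM in the direction the article predicts. The write-up could then present MAR as verified, and part of an apparent benefit could come from who stayed.

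**Working it through.** **1. The plan's own figure.** Inputs from Power and Sample Size: difference 0.3 SD, within-subject correlation 0.5, ratio 3:1, 80% power, type I error 0.05 (taken as two-sided), 20% attrition. With baseline adjustment the variance is 1 − 0.5² = 0.75.

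- Comparison group: (1.96 + 0.84)² × 0.75 / 0.3² × (1 + 1/3) ≈ 87.2, rounded up to 88.
- MM group: 3 × 88 = 264. Total 352, and 352 / 0.8 = 440.

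This matches the stated 352 and 440. The standard error at 12 months is √0.75 × √(1/264 + 1/88) = 0.107 SD. Because 20% attrition is planned, the 5% imputation trigger should be met.

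**2. Can the demographic check see the mechanism?** This was simulated with no true effect, 330 vs 110, and 20% dropout in each group. Comparison dropout was random. MM dropout followed a logistic model on the participant's own 12-month change. Three demographics unrelated to outcome were tested at 5%. The analysis was baseline-adjusted on completers.

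| Log-odds slope per SD | Bias toward MM (SD) | Two-sided false positives |
|---|---|---|
| 0 | 0.00 | 5.5% |
| 0.5 | 0.07 | 11% |
| 1.0 | 0.13 | 26% |
| 1.5 | 0.17 | 41% |

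In every row at least one demographic differed in 14–15% of studies. Chance alone gives 1 − 0.95³ = 14.3%. The check does not respond to the mechanism at all.

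**3. Completers only, one scenario.** MM dropout odds ×2.5 per SD of worse change (18% overall), 20% random dropout in the comparison group, change with SD 1. Over 20,000 simulated studies the mean difference was −0.147 SD (negative favours MM), with false benefit in 22.7% against a nominal 2.5%. Cross-check: about 271 and 88 completers give a standard error of √(1/271 + 1/88) = 0.123. Then 0.147 / 0.123 = 1.20, and P(Z > 1.96 − 1.20) ≈ 22%.

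**4. Imputation, as the plan intends above 5%.**

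- From baseline only, with the final value driving dropout: bias 0.08 / 0.14 / 0.18 SD at slopes 0.5 / 1.0 / 1.5. The ×2.5 odds correspond to a slope of ln 2.5 = 0.92, so the bias is close to that of completers.
- With one interim outcome (assumed correlation with the final value 0.5 / 0.7 / 0.8), dropout driven by the interim outcome: bias about 0, false benefit 2–3%.
- Same imputation, dropout driven by the unseen 12-month value: bias about −0.10 / −0.08 / −0.06 SD. False benefit was 15% / 11% / 8% in one run, and 7–14% across this range in a repeat.

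**5. Range over the unknown gap.** Suppose the 20% of MM participants who leave do worse than MM completers by a gap that the model does not explain, and comparison dropout is random. Then bias = 0.2 × gap.

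| Gap (SD) | Bias (SD) | Share of 0.3 SD | Two-sided false positives |
|---|---|---|---|
| 0.25 | 0.05 | 17% | 8% |
| 0.50 | 0.10 | 33% | 16% |
| 0.75 | 0.15 | 50% | 29% |
| 1.00 | 0.20 | 67% | 47% |

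**6. Which outcomes are exposed.** Table 2 collects the Brief Pain Inventory (BPI), the PROMIS scales and sleep quality quarterly, and Table 1 adds EMA bursts. The Graded Chronic Pain Scale (the example in the power statement), the cognitive battery and telomere length are measured only at baseline and 12 months, so they have no interim value of their own.

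**The case against.** The best defence is that the check gates nothing. Imputation is triggered by the amount of missingness, not by the demographic result, so deleting the sentence would leave imputation and sensitivity analyses in place. The EMA outcomes also go into repeated-measures models that use data up to withdrawal. People who leave for side effects or lack of benefit have usually felt these before leaving, so interim data may capture part of the mechanism. Attrition bias and its direction are disclosed, and retention measures are in place. Imputation variables and tipping-point details are commonly left to a fuller plan.

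Much of this stands, and it limits the point. Three stronger readings should be resisted:

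- A reader might take the 23% as the error rate of the planned analysis. It is not. It belongs to a completers-only analysis, and the plan imputes above 5% missingness.
- A reader might infer that the rule works backwards, withholding MAR when demographics differ. The Missing Data section states no action for that case.
- A reader might infer that sensitivity analyses for departures from MAR are ruled out. The sentence is generic. As worded it addresses the effect of imputing and does not test the MAR assumption, but it does not exclude such a test.

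What does not stand is the criterion itself. It is a stated rule, and no fuller plan can make a demographic comparison evidence for MAR.

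**Conclusion.** The point holds as a wrongly stated criterion, not as proof that the results will be biased. The demographic comparison cannot establish MAR, and in simulation it had no power against the dropout the article anticipates.

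How much bias remains depends on the imputation or mixed model and on what drives dropout. It ranges from about 0, if a modelled interim outcome drives it, through 0.06–0.10 SD toward MM, if the unseen 12-month value does, to about 0.15 SD, half the design effect, if interim outcomes are ignored. These sizes rest on assumptions the documents do not supply: the dropout–outcome link, the interim–final correlation, random dropout in the comparison group and demographics unrelated to outcome. Outcomes measured only at baseline and 12 months are the most exposed.

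**What to change.** - Delete the demographic test as the criterion. Comparisons of those with and without missing data can stay as description.
- State MAR as an assumption conditional on group, baseline outcome, quarterly survey outcomes (BPI, PROMIS), EMA pain, EMA symptoms and MM use, and put these variables in the imputation or mixed models.
- Use the adverse-event scale only when imputing within the MM group. Table 2 (footnote h) gives it to that group alone, so it cannot enter a pooled model. EMA symptoms are collected in both groups and can.
- Prespecify a delta-adjusted (tipping-point) analysis that makes the imputed outcomes of MM dropouts progressively worse, the direction named under Limitations. Report the delta at which each main conclusion changes, including for outcomes measured only at baseline and 12 months.

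The cost is wording and some extra analysis. No new data are needed and the sample size does not change. The Results section says analysis is already underway, so the change should be fixed and dated before group comparisons of outcomes are final.

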### Possible Risks and Discomforts

#### Adverse Events

Adverse events and discomforts may occur due to participation in the study. In the event of adverse events, the PI will determine whether the event is serious and related to the study procedures. If this is the case, the PI will report the event to the NIH and IRB within 72 hours of the event. If the event is not serious, it will be reported to the NIH and IRB during regular status reports.

#### Breach of Confidentiality

Our study will collect data on participants’ medications, including MM. Breaches of confidentiality could occur through communications with participants, loss of research data, or transfer of data.

#### Questionnaires and Interviews

The assessments used in this study address some sensitive issues, such as mental well-being and drug use. The major disadvantages of these assessments are the time required to complete them and the potential breach of confidentiality. Our past experience with these measures indicates that they are acceptable to participants.

#### Cognitive Tests

There are minimal risks associated with these tests. Participants may experience fatigue and feelings of frustration while completing the cognitive function tests. Some participants may also experience stress associated with being tested, though this tends to be quite limited.

#### EMA Surveys

The EMA involves minimal risk as it only collects self-reported data related to participants’ symptoms and their relief, experienced side effects, and other related feelings (eg, anxiety, depression). The major disadvantage of this assessment is the time required to complete daily reports. The possibility of a confidentiality breach is very low because the data collected from the mobile app will be encrypted and pushed to the cloud-based storage database. No data are ever stored on the server’s file system but always in the database. Access to the database is gated, so entry is only permitted to users entering through the approved route (ie, you cannot hack your way into the database by guessing the URL).

#### Pain Sensory Tests

Procedures may be uncomfortable or unpleasant. Participants may experience some temporary discomfort from the pressure and mechanical pain testing. However, if they feel the pain is greater than they wish to tolerate, they can stop any of the procedures at any time.

#### Urine Sample Collection

The risk is minimal for urine sample collection, although some people may experience embarrassment when providing the sample.

#### Blood Collection

The risks of drawing blood from a vein include discomfort at the site of puncture; possible bruising and swelling around the puncture site; rarely, an infection; and uncommonly, faintness from the procedure.

#### Fitbit Data Collection

The risk is minimal when wearing a Fitbit during the EMA period. All data from Fitbit do not include personal identifiers. Data will be stored temporarily on cloud-based storage and will be downloaded regularly onto a secure UF server. Data will be encrypted during the transmission process to ensure security.

#### Anthropometric and Cardiovascular Assessments

The risk is minimal for collecting these measures, including height, weight, blood pressure, and heart rate. Some participants may feel slightly uncomfortable or embarrassed about having some of these measures taken.

## Results

The SMILE study was funded by the NIH/National Institute on Aging in February 2022. Recruitment for the SMILE study began in July 2022 and is expected to continue until 2025, with the last participants recruited completing study involvement in 2026. As of October 2025, we have enrolled 399 participants, with 277 in the MM group and 122 in the comparison group. Data analysis is currently underway, and results are expected to be published starting in 2027. The anticipated timeline for the study is shown in Table 3.

**Table 3. T3:** Study timeline.

Research tasks	2022		2023		2024		2025		2026	
	H1^a^	H2	H1	H2	H1	H2	H1	H2	H1	H2
Recruitment and baseline assessments		✓	✓	✓	✓	✓	✓	✓		
Follow-up assessments (EMA^b^/Fitbit, 1-y visit)			✓	✓	✓	✓	✓	✓	✓	✓
Data/merge analysis and results dissemination				✓	✓	✓	✓	✓	✓	✓

a H1 and H2 indicate the first and second halves of the year.

b EMA: ecological momentary assessment.

## Discussion

### Strengths and Innovation

This project is the first prospective cohort study to comprehensively investigate the IMMPACT-recommended core outcomes [48-50] and cognitive function, using multisource (survey, EMA, sensor, and biomarker) subjective and objective data collected in real time and over 12 months to evaluate the effects of MM use on older adults with chronic pain. This project is innovative in a number of ways.

### Use of Smartphone and Sensor-Based EMA

Mobile technology has rapidly revolutionized health care and research, but it has not yet been widely applied in efforts to investigate the emerging phenomenon of widespread MM use among older adults [45]. This project is the first to leverage both smartphone-based EMA and Fitbit devices to obtain detailed MM use pattern data, as well as subjective and objective real-time measures of pain and functioning in patients’ daily lives. Such data can also provide valuable insights into which MM products are associated with improvements in short-term outcomes [91, 92].

### Enhanced Longitudinal Cohort Design

Our study is the first to leverage a measurement burst design within a cohort study to examine the short- and longer-term effects of MM on older adults. The baseline and 12-month follow-up data will provide comprehensive assessments of pain, functioning, and overall quality of life as snapshots at 2 time points, whereas the quarterly EMA measurement bursts will provide detailed data on short-term variability in pain intensity and physical and emotional functioning, as well as the trajectory of change over 12 months. We will include baseline assessments before participants initiate MM treatment and a comparison group who share similar demographic and health characteristics to reach causal inference.

### Incorporation of Telomere Length as a Measure to Assess MM’s Effect on Cellular Aging Over a 12-Month Period

We and others have shown that telomere length, a measure of cellular aging, is a biomarker of stress-related burdens and buffers [37,38,59,93]. However, no research has investigated how MM may influence cellular aging, as measured by telomere length, in individuals with chronic pain. The proposed study will address this gap by collecting and analyzing telomere length at baseline and after 12 months.

### Consideration of Interpersonal Differences, Including Pain Phenotyping at Baseline

Our study will be the first to examine whether MM’s effects differ based on biological factors (sex and pain phenotyping) and psychological factors (expectancy and social desirability) using established scales [58,76,82]. Such information has valuable implications for physicians and patients regarding which patient subgroups may experience greater benefits from MM use.

### Inclusion of Blood Tests for Multiple Cannabinoids and Associated Metabolites

Our study is the first to test plasma-level cannabinoids and associated metabolites over the course of 1 year for a cohort of older adults with chronic pain. Previous studies have shown that blood tests of cannabinoids and their metabolites can provide valuable information on marijuana use [61-63]. The rich information obtained from repeated blood tests offers objective measures of cannabis exposure to inform how various compounds (eg, THC, CBD) in MM impact health outcomes in this population.

This study will provide valuable scientific evidence to inform physician and patient decisions on using MM as an alternative or supplemental pain treatment option for older adults. With multisource data collected in real time and over 12 months, our results will contribute to the greatly needed evidence on: (1) whether MM can reduce pain and improve physical and emotional functioning in the short term among older adults; (2) whether the effects of MM last for 12 months and demonstrate quality of life improvements; (3) whether health benefits or consequences differ by MM product type; and (4) which subgroups of patients may benefit more from MM use. Should this study confirm that MM helps to improve pain, emotional and physical functioning, and quality of life without significantly reducing cognitive function over a 12-month period, future steps will involve conducting a more focused investigation of specific MM products (eg, sublingual drops with a 1:1 THC:CBD ratio) that are associated with more beneficial outcomes. Future studies are needed to examine treatment side effects as well as optimal dosage to inform more specific recommendations for MM.

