#### Standardized Neurocognitive Assessments at Baseline and 12-Month Visits

After completing the baseline and 12-month follow-up surveys, participants will complete cognitive assessments using the NIH Toolbox Cognition Battery, a standardized neurocognitive assessment tool available as an iPad app [65]. It contains 7 cognition battery tests assessing 5 cognitive subdomains: Language, Executive Function, Episodic Memory, Processing Speed, and Working Memory [65]. Table 1 shows the full list of assessments used. Three composite scores are created from these tests (Fluid, Crystallized, Total Composites), with normative standards available for comparison [86,87]. At the 12-month follow-up visit, only the fluid composite score will be used.

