### Analytical Strategy

#### Power and Sample Size

The total sample size was calculated based on Aims 1 and 2, for which statistical analysis will use a “difference-in-differences” approach. Power was calculated to ensure the detection of differences between the baseline and 12-month follow-up survey in Aim 2, which requires a larger sample size than the intensive longitudinal data from EMA assessments. Assuming a 3:1 ratio of MM versus comparison group and within-subject correlation of variables of 0.5, the sample size required to detect an effect size of 0.3 SD between-group difference (small to medium effect size) [88] in the outcome measured by standardized scales (eg, reduction in pain intensity measured by GCPS), with 80% power (type I error=0.05), is 352 (264 vs 88). Assuming 20% attrition, based on our pilot study (79% retention without a preplanned 12-month follow-up), the final sample size required to achieve the power is 440 (330 vs 110) [89]. For Aim 1, we will have more than 80% power to detect an effect size of 0.3 SD in between-group difference because there will be more repeated measurements in Aim 1. For Aim 3, we will have 264 participants for the analysis since only the MM group will be analyzed. After adjusting for multiple testing with the conservative Bonferroni method [90], the adjusted type I error rate becomes 0.05/7=0.007, under which we will have 99% power to detect the Pearson correlation of 0.3.

#### Aim 1

Aim 1 is to determine whether MM use leads to short-term changes in pain intensity and physical and emotional functioning, as measured in real time by EMA (subjective data) and the Fitbit device (objective data).

Key outcomes of interest include pain intensity, physical functioning, emotional functioning, and sleep. Pain intensity will be assessed from the EMA surveys using self-reported real-time pain intensity on a 0 to 100 visual analog scale. Physical functioning will be assessed from the EMA surveys using self-reported real-time pain interference and from the Fitbit using step counts. Emotional functioning will be assessed from the EMA surveys using self-reported real-time anxiety and depression symptoms (Brief Symptom Inventory).

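### The protocol article counts no significant cognitive reduction as the favourable finding, but a non-significant group difference does not show that there was no decline

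*Protocol article*

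**What the plan says.** The closing paragraph of the Discussion, under the heading on blood tests for cannabinoids, describes the outcome that would lead to studies of specific products. It is that the study confirms benefit on pain, functioning and quality of life "without significantly reducing cognitive function over a 12-month period".

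Cognition is one of many Aim 2 outcomes. It is measured with the NIH Toolbox battery and self-reported change (Aim 2). On the battery, "At the 12-month follow-up visit, only the fluid composite score will be used" (Standardized Neurocognitive Assessments). Aim 2 assigns cognitive tests to generalized linear regression comparing the two groups, as for other measures taken only at baseline and 12 months.

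Power and Sample Size is written for detecting a difference: "the sample size required to detect an effect size of 0.3 SD between-group difference" is given for standardized scales, with reduction in pain intensity as the example. The article does not say how large a cognitive loss the study should be able to rule out.

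**The concern.** A test for harm that fails to reach significance can mean that there is no harm, or that the study was too imprecise to see it. If absence of significance counts as the good result, the two cannot be told apart, and imprecision helps: more dropout or noisier testing makes the favourable reading easier to reach.

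Two features stated in the article push the same way. Group membership stays fixed although participants may start or stop MM at any time (Group Assignment; Population). That would generally dilute a group difference, and for measures taken only at baseline and 12 months Aim 2 describes a group comparison without the time-varying exposure that it gives the intensive data. The Limitations section also accepts that people with side effects may withdraw, which would favour MM.

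At stake is the cognitive statement attached to any report of benefit in adults aged 50 and over. It could read as reassurance while the study's own interval still contains a loss that matters.

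**Working it through.** **Inputs, all from Power and Sample Size.**

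- Allocation and correlation: "Assuming a 3:1 ratio of MM versus comparison group and within-subject correlation of variables of 0.5".
- Difference that the study is sized for: 0.3 SD between groups.
- Power, error rate and completers needed: "with 80% power (type I error=0.05), is 352 (264 vs 88".
- Loss to follow-up: 20%, taken from the pilot study.

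Sidedness is not stated; two-sided is used because it reproduces the sample size.

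**1. Reproduce the plan's figure.** In SD units, the comparison-group size is

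n = (1 + 1/3) × s² × (1.96 + 0.8416)² / 0.3²

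- Baseline-adjusted, s² = 1 − 0.5² = 0.75: n = 87.2, rounded up to 88, so 264 vs 88 = 352. This matches.
- Change score, s² = 2(1 − 0.5) = 1: n = 116.3, rounded up to 117, so 351 vs 117 = 468. This does not match.
- Attrition: 352 / 0.80 = 440. This matches.

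The 352 therefore corresponds to a baseline-adjusted comparison, although the text says that the "statistical analysis will use a “difference-in-differences” approach". Both variants are carried forward.

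**2. Precision at 264 vs 88.** √(1/264 + 1/88) = 0.1231.

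- Baseline-adjusted: SE = √0.75 × 0.1231 = 0.107 SD; half-width 1.96 × 0.1066 = 0.21 SD.
- Change score: SE = 1 × 0.1231 = 0.123 SD; half-width 1.96 × 0.1231 = 0.24 SD.

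An observed difference of exactly zero would leave a 0.2 SD loss inside the interval. Under baseline adjustment, an observed loss of 0.20 SD would be non-significant, with an interval reaching 0.20 + 0.21 = 0.41 SD of loss.

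**3. Chance that a true loss is non-significant.** Power = Φ(loss/SE − 1.96); missed = 1 − power.

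| True loss | Correlation | Baseline-adjusted: power / missed | Change score: power / missed |
|---|---|---|---|
| 0.3 SD (design effect) | 0.5 | 80.4% / 20% | 68.3% / 32% |
| 0.2 SD (assumed) | 0.5 | 46.7% / 53% | 36.9% / 63% |
| 0.2 SD (assumed) | 0.7 (assumed) | 62.4% / 38% | 55.5% / 44% |
| 0.2 SD (assumed) | 0.8 (assumed) | 77.3% / 23% | 72.9% / 27% |

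For a 0.2 SD loss, power passes 50% once the correlation exceeds about 0.56 (baseline-adjusted) or 0.66 (change score).

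**4. Actual enrolment.** Results gives 277 and 122 as of October 2025. With 80% retained, that is about 222 vs 98, and power for 0.2 SD is 47.6% or 37.7%, almost the same as planned.

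**5. What a margin-based reading could deliver.** If the true difference is zero, the chance that the 95% interval excludes a loss of size m is Φ(m/SE − 1.96). At correlation 0.5 this is 80% or 68% for m = 0.3 SD, and 47% or 37% for m = 0.2 SD.

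**The case against.** The strongest reply is that the article contains no decision rule. The sentence is a conditional remark in the Discussion, its consequence is more research, and the next sentence says that side effects still need study. The regression will produce an estimate and an interval, and nothing says that only a p-value will be reported. A margin for one outcome among many is commonly left to an analysis plan, which is not at hand.

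Much of this stands. A reader might infer that MM would be declared cognitively safe on a non-significant test; the article does not say so. A reader might also take cognition to be the main harm endpoint, but the article does not rank it, and adverse events are a separate domain. The absence of a margin is not in itself the defect.

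The numerical objections also have force. The article does not offer 0.2 SD as a meaningful loss. The 0.5 is a generic planning value, not one for the NIH Toolbox. The baseline-adjusted model that reproduces 352 has 80% power at the design effect.

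The wording remains at fault. Under the verb confirm, it makes absence of a significant reduction the favourable finding, and no other sentence says how a null cognitive result would be read. If the word is meant clinically rather than statistically, it still needs a threshold.

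**Conclusion.** The point holds in a limited form. The Discussion treats a non-significant cognitive difference as the finding to hope for, while the study is sized to detect 0.3 SD rather than to exclude a loss. On the protocol's inputs the interval extends about 0.21 SD (baseline-adjusted) or 0.24 SD (change score) either side of the estimate, and a true loss of 0.3 SD would go undetected 20% or 32% of the time.

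It is tempting to add that a modest real loss is more likely missed than found. That follows only for an assumed 0.2 SD loss with the correlation near 0.5, and it reverses above about 0.56 or 0.66. The risk does not vanish there: at an assumed 0.8, 23% to 27% of such losses would still be missed.

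All figures assume unweighted analysis. Inverse probability weighting is described for Aim 1 and not stated for the cognitive regression, so no effect of it is claimed. No error in the planned regression itself is shown.

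**What to change.** Before the cognitive analysis, state the largest acceptable between-group decline in the fluid composite, in SD units. Conclude that there was no meaningful decline only if the 95% confidence interval for the baseline-adjusted MM-minus-comparison difference excludes that decline. Otherwise report the interval and call the cognitive result inconclusive. Reword the Discussion sentence to match.

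This costs a sentence or two and no new data. Results says that data analysis is already underway, so the margin should be fixed and dated now. The downside is that the cognitive result may have to be reported as inconclusive. At correlation 0.5, with no true difference and baseline adjustment, the planned 352 completers would exclude 0.3 SD about 80% of the time but 0.2 SD only about 47% of the time. The choice of margin should rest on what loss matters to patients, not on what the sample can exclude.
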